### Research instruments

#### 5As: stages in the process of smoking cessation

The tobacco cessation research literature strongly supports the use of a comprehensive, clinic-based approach to tobacco cessation, known as the 5A’s— ask, advise, assess, assist, and arrange follow-up. Despite rates of performance of the ask, assess, and advise components of the 5A’s model increasing and being effective, helping and arranging for follow-up components, are far less common [22].

#### Fagerstrom test

The Fagerstrom Test for Nicotine Dependence (FTND) is a widely used and researched short questionnaire [23]. The FTND has been found to have good test-retest reliability, convergent validity, and discriminant validity and performs well from a psychometric perspective with smokers with mental illness as it does with smokers without mental illness [24]. Several studies analysis on the reliability index for the overall score on the FTND indicated that it was excellent (0.87). In 14 studies that evaluated the internal consistency of the FTND, the Cronbach’s alpha coefficient ranged from 0.55 to 0.74, indicating that the FTND has moderate internal consistency [25]. The FTND can be administered in an interview or tobacco users can self-administer the questionnaire. The score ranges from 0 to 10 points, and the mean score of representative samples of smokers is usually in the range of 3–4 points [26].

#### World Health Organization quality of Life-100 questionnaire

The World Health Organization developed the World Health Organization Quality of Life-100 (WHOQOL-100) as a cross-cultural method of assessing QOL separate from a specific disease. Defining quality of life as an “individual’s perceptions of their position in life in the context of the culture and value systems in which they live, and in relation to their goals, expectations, standards, and concerns” [27], the WHOQOL-100 allows the respondent to determine his or her satisfaction while limiting constraints from cultural expectations or developer biases.

The WHOQOL-100 has been validated for use in a mental health population [28].

### Participants’ incentives

Participants were reimbursed Kshs. 200 (approximately USD $2) for transport and time spent at the hospital because of the study.

### Project team

YO was the lead investigator and trained the research assistants, nurses, and counselors who were part of the study.
2 nurses who were part of the hospital staff, who were working at the outpatient registry were recruited to assist in identification of all patients who use tobacco and screened them for eligibility for the study.2 counselors who were not part of the hospital team were trained by YO in tobacco cessation group therapy to lead in facilitation of the group sessions and document the progress and findings.

### Ethical considerations

The research proposal was presented to the department of Psychiatry University of Nairobi (UoN) for study clearance approval. The study and associated protocol were approved by the ethical committee of Kenyatta National Hospital in February 2017. The trial and its protocol were registered in May 2018 by the National Commission for Science, Technology and Innovation (NACOSTI); Permit No: NACOSTI/P/18/37962/21104.

Eligible participants for this study were those who were mentally stable and were in a position to provide informed consent. For those eligible participants who did not understand English nor Kiswahili, a translator was availed for them from a member of the research team trained in responsible conduct of research. If a translator was not readily available, then the participant was given another date to come back when a translator would be available. All participants were briefed on the purpose of the study. The study did not anticipate any more than minimal risk to the participants through their participation because those who had serious withdrawals, as described by the participants, would not be included and would be referred for appropriate interventions. YO is a trained mental health specialist, has been trained in research among vulnerable populations, oversaw the study interventions on site, and participated in facilitating the interventions.

Each screened individual was assured of confidentiality and allowed to ask questions or clarifications prior to participating in the study. Also, participants were enrolled using their client codes to protect their identities, and any identifying information was stored in a password-protected, securely stored file by YO. Considering that the study asked questions that might have made the respondents uncomfortable, those who chose to participate were informed of these risks during the informed consent process for the study, and they were also informed that they had the right to withdraw at any time without any repercussions. The study had safety precautions for participants such that any participant who was found to need further psychological services (e.g. severe withdrawal, confusion, or some form of psychosis) would be referred to the appropriate clinical program or facilities where necessary or advised to seek further management. No such measures were needed.

Dissemination of results is planned through publications in peer-reviewed journals and presentations in scientific conferences. Results will also be disseminated through presentations in local mental health meetings and within the study site. Data sharing maybe considered upon reasonable request.

### Data management and analysis

Data were collected using structured questionnaires and entered into a secure, password-protected database. The hard copy data forms have been stored in a lockable cabinet in lockable office during collection, data entry, analysis, and after study completion. Upon completion of data entry, 20% of hard copy forms will be compared with the entered data to identify systematic or random errors and corrections and repeated data entry will be made appropriately, including 100% recheck if a > 2% error rate is detected.

Sociodemographic characteristics of the study participants, such as age, gender, residence, education level, occupation and perceived health status will be reported. We will also report participants’ health-related quality of life at baseline using the WHOQOL-100 and document participants’ primary mental health disorder. The kind of tobacco product under use, daily amount of tobacco consumption, duration of use, and age of initiation to tobacco will also be described. Using the Fagerstom test, we will determine nicotine dependency and describe intent to quit use of tobacco products. Data on any other substance use such as alcohol, bhang and miraa, including duration of use, will also be reported.

During exploratory data analysis, discrete variables will be summarized using frequencies and percentages, while continuous variables will be summarized using measures of central tendency and dispersion such as means with standard deviations and median with inter-quartile ranges, where appropriate. Bivariate analysis will be carried out to compare the intervention groups with the control groups with respect to socio-demographic characteristics, history of tobacco and substance abuse, type(s) of mental illness, and WHOQOL-100 scores at baseline. Mann Whitney tests will be employed to compare the intervention and control groups where predictor variables are continuous, and chi-squared tests will be applied when the predictor variable is categorical. We will compare unadjusted and adjusted cessation rates at 6 months, recognizing the limitations of the study design at eliminating potential confounders between the two groups given the non-randomized nature of group allocation. Potential confounders include age, sex, baseline tobacco, and baseline type of mental illness, among others. Time to cessation of tobacco use will be compared between the two groups by creating Kaplan-Meier curves and with the creation of corresponding Cox proportion hazard models to determine the effect of the intervention on the primary study outcome. We will report unadjusted and adjusted models, the latter which will aim to control for independent factors associated with relapse. We will perform similar analyses for secondary outcomes as well. All analyses will be carried out using IBM SPSS Statistics Software Version 24, and a two-sided *p* < 0.05 will be used to determine statistical significance.

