#### Group sessions 2–6 (weeks 2–11)

Participants set their anticipated quit date on the 2nd week, which was their second session. During weeks 2 through 11, before the start of the session, feelings of participants were explored, the previous week’s self-reported tobacco consumption or cessation attempt was recorded. The topic of each week was explored first by lecture to explain the topic, and then group members took turns sharing their experiences on the topic.

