#### Group sessions 7–9 (weeks 14–26)

Participants continued attending the CSAT outpatient and ward follow-up programs during this period. Behavioral group sessions 7–9 (weeks 14–26) were conducted once a month by the facilitators whereby each session was begun with a round of discussion on how participants were feeling about their cessation attempts, including any challenges they had experienced. The self-reported amount of tobacco used and quit attempts were documented. The study team also documented the challenges raised and tried to offer practical and supportive therapy for the challenges.

Summary of the group sessions and topics can be found in Table 1.

**Table 1 Tab1:** Group sessions and topics summary

Time Frame	Group sessions
After signed consent	5 As Ask- History of tobacco use Advice- On need to quit tobacco use, and inform on effects of tobacco use Assess- On readiness to quit tobacco use, if not ready use motivational skills to increase readiness Assist- Offer intervention support. Inform on behavioral coping skills and available pharmacotherapies Arrange- Arrange date, time and place of next session to introduce coping skills)
Session 1 (Week 1)	7. Introduction to the program and reasons to quit tobacco use
Session 2 (Week 3)	8. Benefits of quitting and understanding why we smoke and ways of quitting 9. setting quit date
Session 3 (Week 5)	10. Withdrawal symptoms and social support
Session 4 (Week 7)	11. Dealing with stress and anxiety and coping with depression
Session 5 (Week 9)	12. Assertiveness training and anger management
Session 6 (Week 11)	13. Tobacco-free lifestyle and dealing with high risk situations
Follow up sessions (Weeks 14–26)	14. Round of discussion on participants’ feelings, cessation attempts, challenges experienced, and how they coped 15. Documentation of self-reported quit attempts 16. Supportive therapy

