### Control group procedures

The control group was provided questionnaires to fill at the end of Weeks 4, 12, and 26. During the rest of the study, they continued receiving usual care, including clinical care at CSAT. After the conclusion of the study, the control group will be offered the group sessions that the intervention group received.

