### Outcome measures

The study’s primary outcome was self-reported continuous tobacco use abstinence, biochemically verified, at Week 26. It was estimated that the intervention would increase tobacco cessation from the current rate of 15 to 35% [21]. While adjusting for 30% attrition rate, with a sample size of 48 per group, 96 participants would provide 80% power to detect this between-group difference with a two-sided alpha = 0.05.

Secondary outcomes assessed included cessation at Week 4 and 12, number of quit attempts, reduction in number of cigarettes used per day, and health-related quality of life measured at Week 26.

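### The model said to determine the effect on the primary outcome analyses time to cessation, not verified continuous abstinence at Week 26, and no analysis is named as decisive

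*Protocol article*

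**What the plan says.** All references are to the protocol article.

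- **Outcome measures.** The primary outcome is "self-reported continuous tobacco use abstinence, biochemically verified, at Week 26". The same section and the sample size table size the trial on two proportions, 35% against 15%.
- **Data management and analysis.** "Time to cessation of tobacco use will be compared between the two groups by creating Kaplan-Meier curves", together with Cox models, "to determine the effect of the intervention on the primary study outcome". The adjusted models are meant to "control for independent factors associated with relapse".
- **Same section, a few lines before.** "We will compare unadjusted and adjusted cessation rates at 6 months". Potential confounders named there include age, sex, baseline tobacco and type of mental illness.
- **Recording in the intervention arm.** At sessions 2–6, "self-reported tobacco consumption or cessation attempt was recorded". At sessions 7–9, "The self-reported amount of tobacco used and quit attempts were documented".
- **Recording in the control arm.** "The control group was provided questionnaires to fill at the end of Weeks 4, 12, and 26".
- **Baseline and follow-up assessments, and Table 2.** Quit attempts, amount smoked and cotinine results are documented at Weeks 4, 12 and 26.

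The article does not define the event in time to cessation, does not say whether it must be verified, and does not say which records date it.

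**The concern.** The outcome is a status at one time point, but the analysis tied to it by name models how soon people stop. These are different quantities. An ordinary Kaplan-Meier or Cox analysis treats the first cessation as terminal, so later relapse does not undo it. Adjusting for factors associated with relapse adds to the confusion, because relapse is not the event being modelled.

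The planned 6-month cessation rates do fit the outcome. The two analyses can disagree, and the text gives the deciding role, if to either, to the one that does not fit. Follow-up had ended on 28 June 2019, and the analyses are described in the future tense.

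A second, conditional issue is that the intervention arm has more occasions on which a quit can be noted. If those extra records date the event, short quits are caught more often and earlier in that arm, which pushes the hazard ratio towards the intervention.

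**Working it through.** **1. What the trial was sized on.** The printed formula compares two proportions: n = ((r+1)/r) × p̄(1−p̄) × (Zβ+Zα/2)² / (p1−p2)². With r = 1, p̄ = 0.25 and p1−p2 = 0.20, this is 2 × 0.25 × 0.75 × (0.842+1.960)² / 0.04 = 73.6 per group. The table prints 37. That discrepancy is a separate matter; what counts here is that the design is binary, not time-to-event.

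**2. The two endpoints side by side** (ordinary reading of time to cessation):

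| Pattern at Weeks 4 / 12 / 26 | Time to cessation | Primary outcome |
|---|---|---|
| abstinent / abstinent / abstinent, verified | event at Week 4 | success |
| abstinent / smoking / smoking | event at Week 4 | failure |
| smoking / abstinent / smoking | event at Week 12 | failure |
| smoking / smoking / smoking | no event | failure |

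The second and third rows disagree even when both arms are assessed equally often.

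**3. Recording occasions.** Intervention: sessions 2–6 (5, at weeks 3, 5, 7, 9 and 11 in Table 1), sessions 7–9 (3), and Weeks 4, 12 and 26 (3), so up to 11. Control: 3.

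**4. Size of the conditional risk.** Simulation with no true difference and 50 per arm, 1,000 runs per row. Quit hazard = −ln(1−p)/26 per week, where p is the proportion ever quitting by Week 26. Duration of abstinence is exponential. The event is the first recording occasion at which the person is abstinent. Quit rates, relapse rates and the monthly dates (weeks 14, 18, 22) are assumptions.

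| p | Mean abstinence | Events seen, intervention / control | True Week 26 abstinence | Median HR | Log-rank p<0.05 | Week 26 proportions p<0.05 |
|---|---|---|---|---|---|---|
| 0.35 | no relapse | 34.8% / 34.9% | 34.8% | 1.08 | 5.7% | 5.1% |
| 0.35 | 26 weeks | 33.0% / 29.0% | 21.4% | 1.23 | 9.2% | 5.1% |
| 0.35 | 8 weeks | 29.5% / 20.5% | 9.5% | 1.55 | 20.4% | 4.9% |
| 0.35 | 4 weeks | 25.2% / 13.3% | 4.6% | 2.08 | 33.7% | 3.5% |
| 0.60 | no relapse | 59.9% / 60.0% | 59.9% | 1.13 | 11.0% | 4.8% |
| 0.60 | 26 weeks | 56.9% / 49.8% | 35.1% | 1.34 | 23.1% | 5.3% |
| 0.60 | 8 weeks | 51.1% / 34.7% | 14.1% | 1.73 | 46.3% | 4.8% |
| 0.60 | 4 weeks | 43.8% / 23.1% | 6.5% | 2.23 | 63.2% | 4.9% |

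With Weeks 4, 12 and 26 in both arms (no relapse, or mean abstinence 8 weeks), the HR is 1.00 to 1.01 and the log-rank rate 4.9% to 5.3%.

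**5. Dependence on the recording rule.** Weekly quit/relapse process with repeat quits allowed, quit probability 0.02–0.04, relapse probability 0.05–0.20, 50 per arm, 400 replicates, no true difference:

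| Event rule | HR | p<0.05 |
|---|---|---|
| First recorded current abstinence, 11 v 3 occasions | 1.30–1.94 | 10–62% |
| Any quit since last visit, dated to that visit, 11 v 3 | 1.08–1.17 | 5–10% |
| Abstinence lasting to Week 26, 11 v 3 | 1.03–1.09 | 3–7% |
| Weeks 4, 12, 26 in both arms | 0.98–1.00 | 5–6% |

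A repeat with 500 replicates and the log-rank test gave closely similar hazard ratios, but 6% to 16% false positives under the second rule. Using control quit histories therefore reduces the bias without removing it.

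**The case against.** **The schedule bias may never arise.** Cotinine testing is scheduled only at Weeks 4, 12 and 26, and the secondary cessation outcomes are at Weeks 4 and 12. Cessation as this trial measures it plausibly falls at the common weeks. The session notes are part of therapy, and nothing says they feed the Cox model. This stands: a reader might infer that event times are not comparable between arms, but the article supports only a risk that depends on which records are used.

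**The large false-positive rates need several things at once.** Session notes must date the event, transient quits must count, and control quit histories must be ignored, although quit attempts are documented at Weeks 4, 12 and 26. This also stands. With no relapse and 35% ever quitting, the rate is 5.7%.

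**The event is undefined, not wrongly defined.** A sustained-quit definition is possible, and such detail may sit in a fuller document. So the article does not state that relapse is ignored; that is only the ordinary reading of the method named.

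**The matching analysis is already planned.** This is true, so a reader should not infer that the defined outcome goes unanalysed. Nor do the unadjusted and adjusted versions of two analyses amount to four competing tests: reporting both versions is routine.

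What the objections do not remove is the sentence that assigns time-to-cessation models to the primary outcome. That is a statement in the text, not an omission left to an analysis plan.

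**Conclusion.** The point holds as a mismatch between the stated primary outcome and the analysis said to determine the effect on it, with a matching analysis planned alongside and no statement of which decides. This rests on the text alone and needs no simulation.

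The bias from unequal recording is conditional. If session records date the event, the null hazard ratio is about 1.1 to 2.2 over the assumed quit and relapse rates, largest with frequent relapse and current-status recording. It is about 1.0 if only the common weeks are used, and about 1.0 to 1.2 if control quit histories are used or the event is abstinence sustained to Week 26. The documents give no relapse rate, so no single value within these ranges can be preferred.

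Comparing Week 26 proportions in the simulated data of step 4 kept the false-positive rate near its nominal level, at 3.5% to 6.6% including the equal-recording runs.

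**What to change.** In Data management and analysis:

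1. Name the adjusted comparison between groups of the proportion with biochemically verified continuous abstinence at Week 26 as the single primary analysis. The baseline confounders already listed there can serve as the covariates, and the unadjusted comparison is reported beside it.
2. Remove the statement that the Kaplan-Meier and Cox analysis determines the effect on the primary outcome, and make time to cessation secondary or descriptive.
3. If it is kept, use only the Week 4, 12 and 26 assessments in both arms and define the event as the start of abstinence sustained to Week 26. Replace the reference to factors associated with relapse with baseline covariates.

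The cost is wording only: no new data and no extra analysis. The downside is that timing of cessation becomes descriptive. It is also coarse, with three possible event times, and the event can be confirmed only for people followed to Week 26.

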**Table Taba:** 

Ratio of intervention: controls (r)	1
Estimated proportion with improved outcomes in intervention group p_1_	35.0%
Estimated proportion with improved outcomes in control group p_2_	15.0%
Odds Ratio	3.05
Average of proportions (p_1_ + p_2_)/2	0.25
Power (1-α/2)	95%
Power (1-β)	80%
Sample size per group	37
Sample size per group after adjusting for 30% attrition rate	48
**Total sample size**	**96**

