### Baseline and follow-up assessments

During baseline, Age of first use, duration of use, amount used, mental illness managed, Fagerstrom test score, and other substances used were documented. During weeks 4, 12 and 26, Quit attempts made, amount currently being smoked and Cotinine test results were documented. During week 26, the WHOQOL questionnaire was re-administered.

Based on previous tobacco cessation intervention trials, it was assumed that those who did not report abstinence had positive cotinine results.

At the group assessments (Weeks 4, 12, and 26), participants who reported continued tobacco use abstinence and consented to a saliva test were tested using a nicotine cotinine strip (Devon Medical: Nicotine/tobacco test kit). The saliva tests were evaluated by the nurses working at the hospital who were blinded to treatment allocation and were not otherwise part of the study.

The summary of the follow-up assessment activities is reported in Table 2.

**Table 2 Tab2:** Baseline, Follow-up activities and Data to be collected summary

Follow-up time	Activity	Documentation
Week 0 (Baseline)	• Socio-demographic questionnaire • Fagerstrom test for nicotine dependence • WHO quality of life (QOL) instrument	• Age of first use, duration of use, amount used, mental illness managed, other substances used • Fagerstrom test score • WHO QOL score
Week 4	• Explored progress made and documented quit attempts • Focused on challenges experienced and how they were managed • Documented number of sticks currently smoked • Those reporting complete cessation and who gave consent for saliva testing, were then screened using cotinine test	• Quit attempts made • Amount currently being smoked • Cotinine test
Week 12	• Explored progress made and documented quit attempts • Focused on challenges experienced and how they were managed • Documented number of sticks currently smoked • Those reporting complete cessation and who gave consent, were screened using cotinine test	• Quit attempts made • Amount currently being smoked • Cotinine test
Week 26 (Final follow-up)	• Explored progress made and documented quit attempts • Focused on challenges experienced and how they were managed • Documented number of sticks currently smoked • Those reporting complete cessation, gave consent, then were screened using cotinine test • Administered WHO QOL instrument	• Recorded quit attempts made • Amount currently being smoked • Cotinine test • WHO QOL score

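### The plan's cotinine rule, read literally, counts lost participants as tobacco users, while the sizing and default Kaplan-Meier/Cox censoring do not; one rule is needed for Week 26

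*Protocol article*

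**What the plan says.** - **Primary outcome (Outcome measures).** A yes/no status: self-reported continuous abstinence at Week 26, biochemically verified.
- **Scoring rule (Baseline and follow-up assessments).** Citing earlier cessation trials, the article states that "it was assumed that those who did not report abstinence had positive cotinine results". Saliva tests were done at Weeks 4, 12 and 26, only in those who reported abstinence and consented.
- **Sizing (Sample size table; Outcome measures).** "It was estimated that the intervention would increase tobacco cessation from the current rate of 15 to 35" per cent. The table raises 37 per group to 48 in the row "Sample size per group after adjusting for 30% attrition rate". The text repeats this: "While adjusting for 30% attrition rate, with a sample size of 48 per group". The 35% and 15% are not changed for the losses.
- **Analysis (Data management and analysis).** Unadjusted and adjusted 6-month cessation rates are compared. In addition, "Time to cessation of tobacco use will be compared between the two groups by creating Kaplan-Meier curves", and Cox models are to give the effect of the intervention on the primary outcome. No rule is stated for how a lost participant enters these methods.
- **Discontinuation (Limitations of the study).** Participants with severe nicotine withdrawal were referred and taken out of the study.

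**The concern.** The sections imply two treatments of the same people. Someone absent at Week 26 has not reported abstinence. The assessment rule, taken at its word, then makes that person a tobacco user who stays in the denominator. The sizing gives the same person no outcome at all. Kaplan-Meier and Cox as ordinarily run do much the same: they censor at the time of loss, which assumes that the lost would go on to quit at the rate of those still followed.

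That assumption is doubtful here. Discontinuation for severe withdrawal is tied to the difficulty of quitting. The intervention group is described as setting quit dates in group sessions, while controls filled in questionnaires, so loss could also differ between arms.

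At stake are the reported cessation rate in each arm and the absolute benefit, for up to 30 of 100 participants (30% of 50 in each arm). If loss is unequal, the relative effect is at stake too.

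**Working it through.** **Inputs from the Protocol article.** Control 15%, intervention 35%, mean 0.25, ratio 1, two-sided alpha 0.05, power 80%, attrition 30%, 48 per group planned, 50 per group recruited. **Assumptions.** 35% and 15% are rates among those followed; 30% are lost in each arm except in step 5; hazards are constant in step 3.

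**1. The plan's own sample size.** The printed formula gives 2 × 0.25 × 0.75 × (0.8416 + 1.9600)² / 0.20² = 73.6, so 74 per group. The stated 37 appears only if the factor (r+1)/r = 2 is left out (36.8). Then 37 × 1.3 = 48.1, the stated 48. This error is a separate matter, but it is needed to read the power figures in step 6.

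**2. Week 26 rates under each treatment of loss.**
- Lost removed, or censored non-informatively: 35% vs 15%, difference 20 points, risk ratio 2.33, odds ratio 3.05.
- Lost counted as users: 0.35 × 0.70 = 24.5% vs 0.15 × 0.70 = 10.5%, difference 14 points, risk ratio 2.33, odds ratio 2.77.

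**3. How much of the shift is censoring.** Keep the lost in the risk set as non-events, but count quits made before loss. With h = −ln(1 − P) and d = −ln(0.70) = 0.357, the cumulative incidence is h/(h+d) × [1 − exp(−(h+d))].
- Intervention: h = 0.431, giving 29.8%.
- Control: h = 0.163, giving 12.7%. The difference is 17.1 points.

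In the intervention arm the full shift is 35.0 − 24.5 = 10.5 points. Censoring accounts for 35.0 − 29.8 = 5.2. The other 29.8 − 24.5 = 5.3 comes from counting quits made before loss. The binomial standard error for 35% in 50 people is √(0.35 × 0.65 / 50) = 6.7 points, so censoring alone moves that arm's rate by a little under one standard error.

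**4. Relative effect with equal loss.** Under proportional hazards, ln(0.65)/ln(0.85) = 2.65 with censoring. With losses as non-events, the rates 24.5% and 10.5% give ln(0.755)/ln(0.895) = 2.53. The change is small.

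**5. Relative effect with unequal loss (assumed).**

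| Loss, intervention / control | Rates, lost = users | Difference | Odds ratio | Hazard ratio |
|---|---|---|---|---|
| 40% / 20% | 21% vs 12% | 9 points | 1.95 | 1.84 |
| 20% / 40% | 28% vs 9% | 19 points | 3.93 | 3.48 |

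Non-informative censoring would still return 35% vs 15%, hazard ratio 2.65, in both rows.

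**6. Power (two proportions, normal approximation).**

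| Scenario | 48 per arm | 50 per arm |
|---|---|---|
| No loss, 35% vs 15% | 62% | 64% |
| 30% removed, 35% vs 15% | 47% (33.6 left) | 49% (35 left) |
| 30% counted as users, 24.5% vs 10.5% | 44% | 45% |

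Counting the lost as users instead of removing them costs about 4 points.

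**The case against.** **The censoring is inferred, not stated.** The article gives no censoring rule, and Kaplan-Meier and Cox can be run with lost participants kept as non-events. Such detail often sits in an analysis plan, which is not shown here. This stands: a reader may infer that the protocol prescribes censoring at loss, and it does not. What remains is that the default would work against the article's own scoring rule.

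**The scoring rule does not name lost participants.** In its place it may explain only the presumed result of attenders who were not tested. This also stands as a possible reading. The wording nevertheless covers anyone who did not report abstinence.

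**An attrition allowance fixes no denominator.** It is a planning margin, and 35% and 15% come from a cited source that may already count losses as users. In that case the dilution disappears, so the figures above are conditional.

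**Three conflicting treatments?** A reader might count scoring rule, sizing and survival analysis as three. Sizing and default censoring both point to 35% vs 15%, so there are two.

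**Outcome-related loss may be rare.** The Limitations section describes discontinuation for severe withdrawal, but the Ethical considerations section says the referral measures were not needed. The two sections should be reconciled. The number of such losses is unknown.

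**Relative effects barely change.** True with equal loss, not with unequal loss.

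**Conclusion.** The point holds in limited form. The scoring rule, read literally, does not match the sizing or the default behaviour of the survival analysis. The plan run in the usual way would therefore report higher cessation and a larger absolute benefit than its own rule allows: 20 points instead of 14. That rests on 35% and 15% being rates among those followed and on 30% loss in each arm. About half of the intervention arm's 10.5-point shift is due to censoring and the rest to counting quits made before loss.

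Two stronger readings are not supported. One is that the treatment effect as such depends on the choice: with equal loss the risk ratio stays at 2.33 and the hazard ratio moves only from about 2.65 to 2.53. The other is that the scoring of losses takes power from 80% to 45%: most of that gap comes from the sample size error, since 50 per arm gives 64% even with no loss.

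The mismatch should be corrected, mainly for the sake of the reported rates and because nothing in the plan guards against unequal loss.

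**What to change.** 1. Make the Week 26 comparison of verified abstinence the analysis of the primary outcome, with all allocated participants in the denominator and lost or discontinued participants counted as not abstinent.
2. If Kaplan-Meier/Cox is kept, label it supportive and carry lost participants as non-events to Week 26. If quits made before loss count as events, it will still show other rates (29.8% vs 12.7% in the example) than the Week 26 analysis (24.5% vs 10.5%). Say so, or define the event by Week 26 status.
3. Report loss and discontinuation by arm, with one sensitivity analysis restricted to those assessed at Week 26.
4. State whether 35% and 15% already count losses as users. If they refer to those followed, restate power as about 44% at 48 and 45% at 50 per arm. Note that only about 4 points come from the scoring of losses, and that most of the shortfall belongs to the sample size error.

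The cost is a few sentences, recoded follow-up times, and less favourable rates and power. No new data are needed: follow-up is reported as complete, so actual loss by arm can be counted.
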